### Ethical aspects

2.5

The study protocol was approved by the Research Ethics and Biosafety Committees of the National Institute of Public Health (registration number CI: 1713 V47). Informed consent letters were prepared for the parents/legal guardians of the minor participants, and informed assent letters were prepared for the children. Participation will be limited to children who will have both documents signed.

Due to the sensitivity of working with CSA, researchers will first approach school authorities to explain the project’s objective, followed by contact with parents and caregivers to extend invitations. The approach with the children will be carried out by personnel sensitized to CSA and experienced in fieldwork with children. The researchers will explain that the project aims to teach children key information via the IVR headsets to help them take care of their bodies and avoid harm.

Researchers recognize that some children may experience discomfort or anxiety when wearing the IVR headsets. Therefore, the researchers will first ascertain the child’s willingness to participate, even if assent is signed. Second, following the placement of the IVR headsets, the psychology staff and researchers will observe the children’s body language to identify signs of anxiety or discomfort. If a child indicates they no longer wish to participate, the headsets will be removed, and their information will be excluded from the study.

To ensure optimal outcomes, the intervention includes a team of specialized psychologists, trained to work with CSA cases, as the intervention may detect such cases. To this end, strategic partnerships will be stablished with specialized CSA intervention institutions. This collaboration is designed to facilitate appropriate referral of identified abused children to the *Sistema Nacional para el Desarrollo Integral de la Familia* (National System for the Integral Family Development, SNDIF in Spanish). The SNDIF is a decentralized Mexican public agency responsible for providing social assistance and safeguarding the rights of vulnerable populations, including children. Based on the empirical findings of the current intervention, a second phase will focus on developing and implementing targeted training programs. These programs will be delivered to teaching staff and parents to strengthen their capabilities in the detection and appropriate referral of CSA cases to the relevant institutional authorities.

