**Objective:**

This project aims to test the effectiveness of the preventive intervention, “Pinta tu Raya ASI” (Set your Limit LIKE THIS), to prevent CSA. Methods: This is a two-arm matched cluster-randomized controlled trial of an educational intervention to prevent CSA in Mexican elementary school children using Immersive Virtual Reality (IVR). The study will be administered in clusters of public and private schools in urban and rural areas across two Mexican states. The intervention group will receive a learning session with an IVR animation, while the control group will receive the intervention only after the final knowledge acquisition measurement.

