### Intervention and control group

2.3

The study will encompass public, private, urban, rural, and some indigenous elementary schools. Schools will be paired 1:1 prior to randomization based on characteristics like size and locality.

The intervention group will receive an initial learning session involving the IVR animation projected with the Oculus Quest headsets. Groups of 8 to 10 students will be formed for the individual IVR projection (approximately 20-minutes). The projection will take place in a specific area of the school. Headsets will be thoroughly cleaned with a disinfectant solution before each use. Researchers and a team of psychologists will be present during the IVR session.

The control group will not receive the initial learning session but will receive it by the end of the three measurements (Figure 1).

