8) If something happened to you that you are embarrassed, afraid, or ashamed of, would you tell someone you trust?		
Yes	No	I do not Know
9) If someone were to touch you in a way that made you feel uncomfortable and then told you that they would hurt your family, would you tell someone you trust?		
Yes	No	I do not Know
10) Do all children have the right to live free of violence?		
Yes	No	I do not Know
11) Both boys and girls can play with any toy they want, regardless of whether it’s a “boys’ or girls’ toy.		
Yes	No	I do not Know
12) You are such a unique and special person. You are loved just as you are, and you have so much value.		
Yes	No	I do not Know
13) Should you always greet an adult person with a kiss or a hug, even if you feel uncomfortable greeting him or her?		
Yes	No	I do not Know
14) If a grown-up listens to you, believes you, makes you feel happy, takes care of you, and does not hurt you, can we say that they are a person you can trust?		
Yes	No	I do not Know

Three knowledge measurements will be taken in both groups.

Intervention Group: Measurement will be taken prior to the intervention (baseline), immediately after the IVR session, and 15 days later.Control Group: Measurement will be conducted at baseline, followed by two follow-up phases: 20 min after the initial measurement and 15 days later (Figure 1).

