### Statistical analysis

2.7

A descriptive analysis of the baseline characteristics (schools and students) will be conducted. Continuous variables will be reported using the mean and standard deviation. Categorical variables will be presented as frequencies and percentages. We will employ a Propensity Scores matching strategy to create comparable intervention and control groups based on observed baseline covariates.

Following the matching, covariate balance will be assessed using the t-test for continuous variables and the chi-square test for categorical variables. This post-matching evaluation is essential for validating the matching procedure and confirming the similarity of initial group characteristics. The impact of the intervention will be evaluated using a mixed-effects generalized least squares model. This model is specifically selected to address the hierarchical data structure (students nested within matched schools) and the study’s inherent cluster randomized design. The model will include fixed effects at the matched pair level and random effects at the student level. The analysis will also explore subgroup effects by assessing how the intervention’s impact varies across key demographic variables, including school location (rural vs. urban) and school type (public vs. private).

If the percentage of missing data is less than 5%, imputation is not necessary; biases are minimal if the data are mostly Missing Completely at Random (MCAR). The analysis can be performed with complete cases (listwise deletion). If the percentage of missing data is greater than 5%, missing values will be handled primarily by multiple imputation using chained equations (MICE) that account for the hierarchical data structure (school and individual levels). Sensitivity analyses (complete-case, inverse probability weighting, and, if needed, MNAR-based models) will be performed. The proportion of missing data per variable and cluster will be reported. The primary outcome will be analyzed at a two-sided *α* = 0.05. For multiple comparisons, the false discovery rate (FDR, Benjamini–Hochberg) or Bonferroni corrections will be applied as appropriate. All estimates will be presented with 95% confidence intervals and both raw and adjusted *p*-values The whole analysis will be done using Stata 17.0 software (College Station, TX).

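### Children who no longer wish to participate once the headset is on are excluded from the study; before outcomes are complete this can happen only in the intervention arm, and it bypasses the missing-data plan

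*Protocol article*

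**What the plan says.** Section 2.5 (Ethical aspects) anticipates the problem: "Researchers recognize that some children may experience discomfort or anxiety when wearing the IVR headsets". It adds a check before placement, in which "the researchers will first ascertain the child’s willingness to participate, even if assent is signed", and then states the rule for a child who no longer wishes to participate: "the headsets will be removed, and their information will be excluded from the study".

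The timing comes from three other places. For the intervention arm, section 2.4 (Measures and questionnaire) says: "Measurement will be taken prior to the intervention (baseline), immediately after the IVR session, and 15 days later". The headset session therefore falls between the first and second measurements. Control children are measured at baseline, 20 minutes later and 15 days later, with no headset in between. Section 2.3 says of them: "The control group will not receive the initial learning session but will receive it by the end of the three measurements". The abstract agrees: "the control group will receive the intervention only after the final knowledge acquisition measurement".

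Section 2.1 (Study design) randomizes whole schools and takes in all eligible second- and third-grade children.

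Section 2.7 (Statistical analysis) uses complete cases when less than 5% of data are missing and multiple imputation above that. It adds: "Sensitivity analyses (complete-case, inverse probability weighting, and, if needed, MNAR-based models) will be performed". It does not mention the children covered by the rule in section 2.5.

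**The concern.** The rule is a stated instruction about data, so it is not a detail that an article could be expected to leave to the analysis plan. It acts after allocation, and its expected trigger is discomfort or anxiety from the intervention itself. During the measurement period control children have no comparable event, so those who would have reacted in the same way stay in the comparison.

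The estimate then sets intervention children who were willing to continue against all control children. That is not the comparison the randomization set up. The planned imputation, weighting and MNAR analyses work on records with absent values. A child whose whole record is excluded, baseline included, is not such a record. That child counts neither towards the 5% threshold nor in the missing-data proportions that section 2.7 promises per variable and cluster.

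**Working it through.** **1. Which arm can trigger the rule before outcomes are complete?**

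| Step | Intervention | Control |
|---|---|---|
| Baseline questionnaire | yes | yes |
| Headset session | after baseline | none yet |
| Second questionnaire | immediately after the session | 20 min after baseline |
| Third questionnaire | 15 days later | 15 days later |
| Headset session | already given | after the third questionnaire |

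Only the intervention arm can.

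**2. A yardstick for size.** Section 2.1 gives 324 children and 12 schools per arm, an intraclass correlation of 0.15 and 80% power at 0.05 (two-sided in section 2.7). The means and SDs used are not given, so 324 cannot be reproduced independently. It can be inverted:
- children per school: 324 / 12 = 27
- design effect: 1 + (27 − 1) × 0.15 = 4.9
- effective number per arm: 324 / 4.9 = 66.1
- standard error of the difference in SD units: √(2 / 66.1) = 0.174
- implied detectable difference: (1.960 + 0.842) × 0.174 = 0.487 SD (0.510 with a t reference on 22 degrees of freedom)

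As a coherence check, a difference of 0.4873 needs 66.11 independent children per arm. The fixed-cluster formula then gives 66.11 × 0.85 / (12 − 66.11 × 0.15) = 26.96 per school, rounded up to 27, and 27 × 12 = 324.

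**3. Bias from exclusion.** Let q be the share of intervention children excluded. Let g be the mean outcome of retained children minus the mean that excluded children would have had, in SD units. The full-arm mean is (1 − q) × retained + q × excluded, so the retained mean differs from it by q × g. Neither q nor g is in the article; the values below are assumptions. The type I error is two-sided, under no true effect, with standard error 0.174.

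| q | children of 324 | g (SD) | bias (SD) | % of 0.487 | type I error |
|---|---|---|---|---|---|
| 2% | about 6 | 0.5 | 0.010 | 2.1 | 0.050 |
| 5% | about 16 | 0.5 | 0.025 | 5.1 | 0.052 |
| 5% | about 16 | 1.0 | 0.050 | 10.3 | 0.060 |
| 10% | about 32 | 0.5 | 0.050 | 10.3 | 0.060 |
| 10% | about 32 | 1.0 | 0.100 | 20.5 | 0.089 |

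The table takes g as positive, which inflates the effect. With g negative the bias has the same size and dilutes the effect.

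**4. Power.** Excluding 5% or 10% of the intervention arm moves power from 80% to 79.8% or 79.6%. The issue is bias, not precision.

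**The case against.** **The trigger is withdrawal, not distress.** The sentence applies to a child who no longer wishes to participate. It stands in the ethics section of an approved protocol and concerns young children. Visible anxiety alone excludes nobody. This stands, and it limits the point: where a child or guardian wants the data removed, removal may be right. But the sentence draws no line between taking the headset off and leaving the study, so a child who wants only the first is treated as wanting both.

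**The rule is not limited to one arm.** Read literally, a control child who stops at the delayed session would be excluded too. The article does not say this is intended. If it were, it would discard outcomes already measured and would not restore the randomized comparison, because the two exclusions happen at different times and under different circumstances.

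**Propensity-score matching may rebalance the arms.** Section 2.7 plans matching on observed baseline covariates, and knowledge is measured at baseline. Matching or adjustment could shrink the gap to the part that baseline does not explain, so q × g is the unadjusted figure. Neither can recover deleted records or balance unmeasured tolerance of the headset.

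**Stronger readings that the article does not support.** A reader might infer that the bias favours the intervention. Nothing in the article links wanting to stop with knowledge scores, so the direction is open. A reader might also infer that counts of distressed children will be lost. The excluded information may mean questionnaire data only, and a full protocol may keep a tally of stopped sessions; the article names none but does not rule one out.

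**Conclusion.** The point holds. Section 2.5 fixes a rule that removes randomized children after allocation for a reaction to the intervention. Before outcomes are complete it can act in one arm only, and it places those children outside the missing-data plan of section 2.7. This rests on the stated wording and timing, not on any assumed rate.

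The size does rest on assumptions. It is negligible if few children stop: 0.025 SD at 5% excluded with a 0.5 SD gap, about one seventh of the standard error of 0.174. It becomes material only towards 10% with a 1 SD gap, where it reaches 0.10 SD, about a fifth of the implied detectable effect, and type I error rises to about 0.089. That effect of about 0.49 SD is itself back-calculated from 324 per arm. The documents support neither a claim that the result will be inflated nor a claim that the distortion will be large.

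**What to change.** Leave headset removal and the child's right to stop as they are. Reword section 2.5 to separate two events:

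- **Stops the headset session.** Keep the baseline record. Offer the remaining questionnaires only if the child still assents. Analyse the child in the school's allocated arm, and treat absent scores as missing under section 2.7.
- **Withdraws from the study or asks for data removal.** Collect nothing further. Remove data already collected only when the child or guardian asks for it.

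State also that a control child's stopping at the delayed session does not remove outcomes already measured. Report the number of stopped sessions and the number of data withdrawals, by arm and school.

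The cost is a wording change to the protocol and to the consent and assent letters, which needs ethics review, and a few more questionnaires from children who are still willing. The sample size needs practically no change. The change should be made before the first sessions, because excluded records may not be recoverable.

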### Data management

2.6

The information of the questionnaires will be stored in a password-protected Excel file, and only the research team will have access to this document. To ensure the confidentiality and security of student information, children will not be identified by name. Instead, an alphanumeric code will be created based on their state, school, grade, and classroom.

### Statistical analysis

2.7

A descriptive analysis of the baseline characteristics (schools and students) will be conducted. Continuous variables will be reported using the mean and standard deviation. Categorical variables will be presented as frequencies and percentages. We will employ a Propensity Scores matching strategy to create comparable intervention and control groups based on observed baseline covariates.

Following the matching, covariate balance will be assessed using the t-test for continuous variables and the chi-square test for categorical variables. This post-matching evaluation is essential for validating the matching procedure and confirming the similarity of initial group characteristics. The impact of the intervention will be evaluated using a mixed-effects generalized least squares model. This model is specifically selected to address the hierarchical data structure (students nested within matched schools) and the study’s inherent cluster randomized design. The model will include fixed effects at the matched pair level and random effects at the student level. The analysis will also explore subgroup effects by assessing how the intervention’s impact varies across key demographic variables, including school location (rural vs. urban) and school type (public vs. private).

If the percentage of missing data is less than 5%, imputation is not necessary; biases are minimal if the data are mostly Missing Completely at Random (MCAR). The analysis can be performed with complete cases (listwise deletion). If the percentage of missing data is greater than 5%, missing values will be handled primarily by multiple imputation using chained equations (MICE) that account for the hierarchical data structure (school and individual levels). Sensitivity analyses (complete-case, inverse probability weighting, and, if needed, MNAR-based models) will be performed. The proportion of missing data per variable and cluster will be reported. The primary outcome will be analyzed at a two-sided *α* = 0.05. For multiple comparisons, the false discovery rate (FDR, Benjamini–Hochberg) or Bonferroni corrections will be applied as appropriate. All estimates will be presented with 95% confidence intervals and both raw and adjusted *p*-values The whole analysis will be done using Stata 17.0 software (College Station, TX).

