### Study design

2.1

This study is a two-arm matched cluster-randomized controlled trial that includes the psycho-pedagogical intervention “Pinta tu Raya ASI.” The intervention targets second and third-grade students (ages 7–8) in elementary schools in the Mexican states of Morelos and Nayarit. This initiative is part of a comprehensive two-year study. (Figure 1).

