**Figure 1 fig1:**
[figure not shown]
Study design.

For school selection, a list will be requested from the Ministry of Education, focusing on municipalities with a gender violence alert designation. This designation indicates emergency governmental actions to confront and eradicate femicide and the disappearance of women. A random sampling of schools will then be conducted from this list. Prior to randomization, schools will be paired 1:1 based on specific characteristics (e.g., size, type, locality).

The required sample size for the intervention was calculated using the clustersampsi command from the STATA statistical software package, which is designed for estimating sample sizes in cluster randomized trials. The mean knowledge scores (and standard deviations) of the control and intervention groups were included, setting the number of clusters at 12 schools per arm (due to the operational capacities of the work team) (33). The intraclass correlation value was set at 0.15 (34), the power at 80%, and the statistical significance at 0.05. This resulted in a minimum sample size of 324 children per arm. Following the selection of the participating elementary schools, the randomization unit will be the schools as a whole. Specifically, all eligible children in the second and third grades within a selected school will participate in the study.

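### Propensity-score matching of the arms is planned in a trial that already pairs and randomises schools; it is unnecessary, puts the randomised comparison at risk, and is checked with tests that are not a valid balance criterion

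*Protocol article*

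**What the plan says.** Section 2.1 (Study design) of the protocol article describes the design: "This study is a two-arm matched cluster-randomized controlled trial". On the order of steps it says: "Prior to randomization, schools will be paired 1:1 based on specific characteristics (e.g., size, type, locality"). It then says that "the randomization unit will be the schools as a whole" and that "all eligible children in the second and third grades within a selected school will participate in the study". Section 2.3 repeats that pairing comes before randomisation.

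Section 2.7 (Statistical analysis) adds a second matching step, after the baseline description and before the impact model: "We will employ a Propensity Scores matching strategy to create comparable intervention and control groups based on observed baseline covariates". The check on it is: "Following the matching, covariate balance will be assessed using the t-test for continuous variables and the chi-square test for categorical variables". The article gives that check a formal role: "This post-matching evaluation is essential for validating the matching procedure and confirming the similarity of initial group characteristics".

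The impact model comes next. It refers to students nested in matched schools and has fixed effects for the matched pair and random effects for the student.

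The article does not say whether children or schools are propensity-matched, whether matching stays within the randomised pairs, which ratio or caliper applies, or what happens to unmatched children.

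**The concern.** A propensity score is the modelled probability of being in the intervention arm given covariates. It is a tool for studies in which allocation was not controlled. Here allocation is random within school pairs, so any difference between the arms at allocation is chance. Regression adjustment handles chance differences without changing who is analysed.

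Three things are at stake.

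- **Analysed set.** The matching precedes the only impact analysis described. Who enters that analysis may then depend on the covariates, caliper and ratio chosen after allocation is known.
- **Pair structure.** Matching on a pooled score ignores the randomised pairs. The matched-pair term in the impact model could then mean either the randomised school pair or the propensity pair.
- **Balance check.** The t and chi-square tests treat children as independent, yet they are meant to validate the matching.

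**Working it through.** **1. Is this just the pre-randomisation pairing under another name?** Set side by side, the two steps differ. Section 2.1 pairs schools on size, type and locality before randomisation. Section 2.7 matches intervention and control groups on observed baseline covariates. A propensity score can be fitted only once allocation is known. The two are therefore separate steps.

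**2. Inputs.** From section 2.1: 12 schools per arm, minimum 324 children per arm, ICC 0.15, power 80%, significance level 0.05 (two-sided per section 2.7). The means and SDs behind 324 are not printed, so 324 cannot be reproduced, only inverted:

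- children per school m = 324/12 = 27
- design effect = 1 + (27 − 1) × 0.15 = 4.90
- effective number per arm = 324/4.90 = 66.1
- implied detectable difference = (1.96 + 0.842) × √(2 × 4.90/324) = 0.487 SD

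**3. Children dropped and pairs crossed (illustration).** Assumed: 1:1 nearest-neighbour matching of children, without replacement, on a score pooled over all schools.

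| Assumption | Children dropped |
|---|---|
| 0.2 SD caliper, 3–5 child covariates, equal arms | about 13–17% |
| 0.2 SD caliper, 3 covariates, pairing explains half the ICC, unequal school sizes | about 12% |
| No caliper, equal arms | none |
| No caliper, unequal school sizes | about 3% |

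If matching ignores the 12 pairs, a child meets a partner from its own pair about 1 time in 12, so 11/12 ≈ 92% cross pairs. Simulation gives about 91%. Matching only within pairs would cross none. Re-matching whole schools 12:12 without a caliper would drop no one.

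**4. Power.** With a fraction f kept in every school, m = 27f, n = 324f and power = Φ(0.487/√(2[1 + (m − 1) × 0.15]/n) − 1.96).

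| f | n per arm | Design effect | Power |
|---|---|---|---|
| 1.0 | 324 | 4.90 | 80.0% |
| 0.9 | 291.6 | 4.495 | 79.2% |
| 0.8 | 259.2 | 4.09 | 78.3% |
| 0.7 | 226.8 | 3.685 | 77.1% |

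The loss is small because the 12 schools per arm dominate the variance.

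**5. Balance tests.** Before any matching, a nominal 5% test that ignores clustering rejects by chance with probability 2[1 − Φ(1.96/√DEFF)].

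- Covariate ICC 0.15: DEFF 4.90, rate 37.6%
- Covariate ICC 0.05: DEFF 1 + 26 × 0.05 = 2.30, rate 19.6%

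The covariate ICC is an assumption; 0.15 is the article's value for the outcome. Pairing that explains half of an ICC of 0.15 lowered the first rate to 25% in simulation.

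The article, however, tests after matching. Simulated after 1:1 matching with a 0.2 SD caliper:

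- covariates in the score: 0% flagged
- covariates outside the score, ICC 0.15: about 31–35% flagged
- the same, if pairing explains half the ICC: about 23% flagged

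In neither case does the p-value measure balance. For matched covariates the pass is built in; for the others, clustering drives the rejections.

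**The case against.** The strongest reply is that the article never says children are dropped or pairs are broken. It still has a matched-pair effect in the model, and the school is the only matched unit the model description names. Algorithm and caliper are details that an article may leave to a fuller document. A supporter might add that consent can disturb balance even in a randomised cluster trial.

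Much of this stands, and it limits the point. A reader might infer more than the document supports in four ways:

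- **That the matching discards children and breaks the pairs.** Both are likely under ordinary pooled child-level matching, but neither is stated, and within-pair or whole-school matching would avoid some of it.
- **That the analysed number falls below 324 per arm.** That figure is a minimum. All eligible children in the selected schools take part, so enrolment may exceed it.
- **That the tests will often flag chance imbalance and set off repeated re-matching.** The article describes one balance evaluation and no re-matching. The rates of about 20% and 38% belong to the unmatched sample; with caliper matching, the matched covariates were not flagged at all.
- **That lost power is the main harm.** It costs at most about 3 percentage points at 70% retention.

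The reply does not remove the core. Propensity matching is an affirmative statement of method, not an omitted detail, and it precedes the impact analysis. If recruitment imbalance is the worry, covariate adjustment deals with the observed part of it without dropping anyone.

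**Conclusion.** The point holds in this form: the article plans propensity-score matching of arms that pair-matched randomisation has already made comparable. The step is unnecessary, may remove randomised children, may override the school pairs, and leaves the meaning of matched pair in the impact model open.

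Under pooled child-level matching the illustrative size is 0% to about 17% of children dropped, depending mainly on the caliper, and about 90% of matched children linked across randomised pairs. These figures rest on an assumed algorithm, 3 to 5 child covariates and a covariate ICC of 0.15. The conclusion that the step is unneeded and weakens the randomised comparison does not depend on them.

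The unclustered t and chi-square tests are not a valid balance criterion, whether they pass or fail. Because the matching could decide who enters the only impact analysis described, the text should be changed before any outcome data are analysed.

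**What to change.** In section 2.7, and in any analysis plan:

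1. Remove propensity-score matching and the post-matching significance tests from the impact analysis. If a propensity-score analysis is wanted, label it a sensitivity analysis and prespecify its level, covariates, algorithm and handling of unmatched children.
2. State that the impact analysis includes all randomised children by allocated school, within the 12 original randomised pairs, with clustering represented at school level. Define matched pair as the pair formed before randomisation.
3. Adjust for a short prespecified covariate list that includes the baseline knowledge score.
4. Describe baseline balance by arm with means, percentages and standardised differences, without significance tests.

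The cost is wording only. No design, recruitment or data-collection step changes, and the analysis becomes simpler.

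### The impact model's listed terms leave out the school within pair, the unit randomised; with model-based standard errors the 5% test is anticonservative, by an amount that depends on the contrast and the pairing

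*Protocol article*

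**What the plan says.** Under Study design, the article states that "the randomization unit will be the schools as a whole". On matching it says: "Prior to randomization, schools will be paired 1:1 based on specific characteristics". The sample size was obtained by "setting the number of clusters at 12 schools per arm", and "The intraclass correlation value was set at 0.15 (34), the power at 80%, and the statistical significance at 0.05". The result is a minimum of 324 children per arm.

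Under Measures and questionnaire, each child in both arms is measured three times: at baseline, shortly afterwards, and 15 days later.

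Under Statistical analysis, the impact model is a mixed-effects generalised least squares model, said to have been selected because students are nested in matched schools and the trial is cluster randomised. Its terms follow: "The model will include fixed effects at the matched pair level and random effects at the student level". The section names no school random effect, cluster-robust variance or school-level analysis for this model. School level appears only in the imputation model and in the reporting of missing data.

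**The concern.** Each pair holds one intervention school and one control school. A pair fixed effect removes what the two schools share. It leaves untouched the difference between them, and that difference is the contrast that estimates the arm effect. A student random effect handles repeated scores from one child; it says nothing about two children in the same school. Given the pair, the listed terms therefore treat children of one school as independent.

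This conflicts with the purpose the article gives for the model and with the intraclass correlation used to size the trial. At stake are the p-value and confidence interval of the main result: a session with no effect on knowledge would be declared effective more often than 5% of the time. The article intends positive results to support replication in other states.

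**Working it through.** **Inputs from the article.** 12 schools per arm, hence 12 pairs; 324 children per arm, hence 324/12 = 27 per school; intraclass correlation 0.15; two-sided 5% level.

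**Assumptions not in the article.** Total variance 1 (results in SD units), equal school sizes, pairs meaning the pre-randomisation school pairs, model-based standard errors with a normal reference, and the share of school variance that pairing explains (varied below).

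**The plan's own sample size.** Design effect = 1 + (27 − 1) × 0.15 = 4.9, so 324 children carry the information of 324/4.9 ≈ 66. The article does not print the means and SDs, so 324 cannot be reproduced, only solved backwards: (1.96 + 0.842) × √(2 × 4.9/324) = 2.802 × 0.174 ≈ 0.487 SD. The standard error behind that sample size is thus 0.174 SD.

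**Post-intervention comparison.** Let s be the school variance left inside pairs.

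- True variance of the arm difference: (2/12) × (s + 0.85/27).
- Residual mean square after pair fixed effects and arm, without a school term: [12 × 2 × 26 × 0.85 + 11 × 13.5 × 2(s + 0.85/27)] / 635, where 635 = 12 × 53 − 1.
- Variance that the model reports: residual mean square × 2/324.
- Type I error: 2 × [1 − Φ(1.96 × model SE/true SE)].

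With s = 0.15 (no gain from pairing), the true SE is √[(2/12) × 0.1815] = 0.174, the same as in the sample size. The residual mean square is (530.4 + 53.9)/635 = 0.920, so the model SE is √(0.920 × 2/324) = 0.075. The ratio is 0.433 and the type I error 2 × [1 − Φ(0.849)] = 39.6%.

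| School variance explained by pairing | s | True SE | Model SE | Type I error |
|---|---|---|---|---|
| none | 0.15 | 0.174 | 0.075 | 39.6% |
| 30% | 0.105 | 0.151 | 0.075 | 33.3% |
| 50% | 0.075 | 0.133 | 0.074 | 27.7% |
| 80% | 0.03 | 0.101 | 0.073 | 15.7% |

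Simulation agrees (about 39%, 33%, 28% and 16%).

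**Change from baseline.** School effects that do not change over time cancel. What matters is the school share c of change-score variance, for which the article gives no value. With s replaced by c and 0.85 by 1 − c:

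| School share c | Type I error |
|---|---|
| 0 | 5.0% |
| 0.01 | 8.2% |
| 0.02 | 11.4% |
| 0.05 | 20.2% |
| 0.10 | 31.5% |

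Simulations agree to about one percentage point.

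**Other contrasts** (simulation, student variance 0.35 assumed, school effects constant over time, pairing explaining from 80% to none of the school variance). Adjusting a follow-up score for baseline gives about 8% to 22%. Pooling two follow-up rounds gives about 20% to 47%.

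**A valid comparator.** A paired t-test on the 12 within-pair differences in school mean, with 11 degrees of freedom, rejects in about 4% to 6% of simulated null trials in every scenario.

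**The case against.** The strongest reply is that the article does not fix enough to attach a number. It measures every child three times, and a student random effect serves a purpose only if those repeated scores are modelled. A change or baseline-adjusted contrast is then at least as natural as a comparison of single post-intervention scores. Under a change contrast with stable school effects the inflation disappears. The 0.15 is a planning value, and the gain from pairing is unknown. This stands: it is why every figure above is conditional.

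A second reply is that a condensed article may leave the variance estimator to a fuller document, and that school-clustered standard errors could accompany the listed terms. Such errors, with a small-sample correction, would indeed resolve the matter, so the anticonservative result is tied here to model-based standard errors. But the article does more than stay silent. It spells out the fixed and random terms as the way the clustering is addressed, and they do not address it.

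A third reply is that the matched pairs might be those of the propensity score step described just before. The wording allows this. Nothing in the article says that such pairs would account for correlation within schools, so the gap remains.

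**Conclusion.** The point holds: the stated terms do not account for correlation among children of one school within a pair, contrary to the model's stated purpose, to the unit of randomisation and to the intraclass correlation in the sample size. With model-based standard errors the 5% test is anticonservative whenever school-specific variation remains in the contrast.

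A reader might infer that the trial's type I error is 16% to 39%. The documents do not support that as an unconditional statement. The range belongs to a post-intervention comparison with intraclass correlation 0.15, 27 children per school, and pairing that explains from 80% to none of the school variance. The article states neither the contrast nor the gain from pairing. A change contrast can lie near 5%, though only if schools do not differ in their change over time; small school shares (0.01 to 0.10) already give about 8% to 31%. Nor can one conclude that the standard errors will certainly be far too small, since the variance estimator is not stated. What is certain is that the sentence needs correcting before analysis, because the main p-value and interval depend on it.

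**What to change.** Replace the sentence on model terms with: pair fixed effects, a random intercept for school, and a random intercept for child within school, plus a random school-by-round effect if all three rounds are modelled. Test the arm effect with small-sample degrees of freedom, about 11 for 12 pairs (for example Satterthwaite or Kenward–Roger). The correction matters even with the right standard error: referring a t statistic on 11 degrees of freedom to the normal cut-off of 1.96 rejects 7.6% of the time.

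Two alternatives are equally acceptable: school-clustered standard errors with a small-sample correction, since there are only 24 schools, or a paired analysis of the 12 within-pair differences in school mean. Running the paired analysis as an additional check is optional. It would help to name the primary contrast in the same sentence and to say that pairs means the school pairs formed before randomisation.

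The cost is a wording change and no new data. Confidence intervals will be wider, in line with the clustering the sample size already assumes.
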